### Registration

2.6

This study will be performed from June 2022 to May 2024 at Hiroshima University Hospital. Trial Registration number: jRCTs062220013; pre-results.

## Discussion

3

In this clinical trial, we will examine the usefulness of percutaneous neck interferential current sensory stimulation for patients with PD. Hypoesthesia of the pharynx and larynx is a particular characteristic of PD [4]; therefore, we will mainly measure the cough reflex as the primary endpoint. However, PD leads to various swallowing disorders, requiring the use of numerous instruments for evaluation. We will measure the tongue pressure to assess the oral cavity function because low tongue pressure indicates dysfunction of the oral phase of swallowing in many neurological diseases [20,21]. In patients with acute stroke, basal ganglia lesions are associated with delayed swallowing reflex [22]. The presence of abnormal basal ganglia is a characteristic of PD; thus, we will examine the delayed swallowing reflex via videofluoroscopic examination. Since interferential current stimulation could affect the central pattern generator and sensory nerve, an improvement in the swallowing reflex can be expected. Moreover, drooling or sialorrhea and dementia have attracted attention as clinical predictors of dysphagia in patients with PD [23]. Cervical interferential current stimulation is also effective for patients with dysphagia and dementia. We will determine the relevant risk factors for dysphagia in patients with PD and contributory factors of interferential current stimulation [24].

Moreover, this study will use novel instruments, such as multichannel surface electromyography and electronic stethoscope, to evaluate swallowing function in patients with PD. Multichannel surface electromyography can evaluate the recruitment of motor units and the effect of electrical stimulation [25,26]. Recently, electronic stethoscopes have been developed for the evaluation of swallowing sounds with the help of artificial intelligence [27]. These novel methods of evaluation can provide new insights on dysphagia in patients with PD and the usefulness of percutaneous neck interferential current stimulation. However, this exploratory study is limited by the single-arm, open-label design and small sample size.

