### Study design

2.2

The first draft of the study protocol, of a single-arm, open-label study, was finalized on February 28, 2022, and the draft adhered to the SPIRIT reporting guidelines [16]. The second amended draft was finalized on December 31, 2022. We designed the study to determine the efficacy and safety of percutaneous neck interferential current sensory stimulation for patients with PD, diagnosed according to the Movement Disorder Society criteria, of Hoehn–Yahr stages 2–4 at Hiroshima University Hospital [17]. This study aims to identify the factors associated with swallowing dysfunction and determine the safety of neck percutaneous interferential current sensory stimulation. Therefore, neither randomization nor blinding was used in this study design. The patient inclusion and exclusion criteria are presented in Table 1.

**Table 1 tbl1:** Eligibility criteria.

Inclusion criteria
1. Diagnosis of clinically probable or established PD based on the Movement Disorder Society criteria 2. PD of Hoehn–Yahr stages 2–4 at the time of registration 3. Levodopa dosage remaining unchanged for more than 1 month 4. Age >19 and < 86 years 5. Able to visit the hospital twice a week 6. Able to provide written informed consent

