### Sample size

2.3

We calculated the required sample size according to preliminary cough tests among patients with neurodegenerative disorders. The proportion of patients with a normal cough reflex after the 1% citric acid challenge required was 28.6%. Assuming that the proportion of patients with a normal cough reflex after 8 weeks of therapy will be 50%, a sample size of 27 participants was estimated, based on an alpha level of 0.10, power of 0.80, and 10% dropout rate.

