### Data acquisition

2.4

Clinical evaluation and diagnosis will be confirmed by two neurologists (MN and HY). The following data will be recorded: body height, weight, body mass index, grip power, calf circumference, disease duration, past medical history, habits of alcohol drinking and smoking, blood pressure, heart rate, oxygen saturation, Unified Parkinson's Disease Rating Scale score [18], medication, Functional Oral Intake Scale score, Eating Assessment Tool-10 score, and blood test values [19]. Cough test, tongue pressure, and peak expiratory flow will be investigated as previously reported [5,20]. Moreover, novel methods, including multichannel surface electromyography, electronic stethoscope, and artificial intelligence system, will be applied. The data will be stored in the Redcap, Electronic Data Capture system. Author YH, who will be blinded to the acquired data, will independently monitor and audit the stored data every week.

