### Data analysis and statistical methods

2.5

Safety analysis will include an evaluation of the proportion of patients with skin symptoms and of exacerbation of neurological symptoms in the head and neck due to the electrical stimulation. If these symptoms are found, the therapy will be discontinued. To assess primary and secondary endpoints, the swallowing status of each patient at the time of the initial intervention will be compared with that at the end of the intervention (8 weeks from the initiation of the intervention) or at 8 weeks after the end of the intervention (16 weeks from intervention initiation). Statistical analysis will be performed using JMP statistical software version 16 (SAS Institute Inc., Cary, NC, USA). As appropriate, the statistical significance of intergroup differences will be assessed using χ^2^ test, Mann–Whitney *U* test, or unpaired *t*-test. We will consider p < 0.05 reflective of statistical significance.

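### A single-arm trial cannot determine contributory factors of the stimulation, and with about 24 to 27 patients any factor search judged at p<0.05 can only explore

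*Protocol article*

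**What the plan says.** Section 2.2 (Study design) gives an aim: "This study aims to identify the factors associated with swallowing dysfunction and determine the safety of neck percutaneous interferential current sensory stimulation". The next sentence draws from this the reason for having neither randomization nor blinding.

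Section 3 (Discussion) goes further: "We will determine the relevant risk factors for dysphagia in patients with PD and contributory factors of interferential current stimulation". That is two sets of factors, one for dysphagia and one for the stimulation.

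Section 2.5 (Data analysis and statistical methods) says that, as appropriate, "the statistical significance of intergroup differences will be assessed using χ^2^ test, Mann–Whitney *U* test, or unpaired *t*-test", and adds one threshold without exception: "We will consider p < 0.05 reflective of statistical significance".

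Section 2.4 (Data acquisition) lists what will be recorded, beginning with "body height, weight, body mass index, grip power, calf circumference, disease duration, past medical history, habits of alcohol drinking and smoking" and continuing through vital signs, the Parkinson's disease rating scale, medication, swallowing scales and blood tests. Cough test, tongue pressure and peak expiratory flow are also measured.

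Section 2.3 (Sample size) rests on the cough-reflex proportion alone: "a sample size of 27 participants was estimated, based on an alpha level of 0.10, power of 0.80, and 10% dropout rate". The Abstract and the Discussion both call the study exploratory and name the single-arm, open-label design and small size as limitations.

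**The concern.** There are two separate problems.

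The first is one of design. Calling a variable a contributory factor of the stimulation means that the effect of the stimulation differs with that variable. In a single arm, only change from baseline is observed, and change mixes any effect of the stimulation with spontaneous change and retest change. A variable that predicts change may predict any of these. No choice of test or model removes the ambiguity, because the comparator that would resolve it does not exist.

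The second is one of error rates, and applies to both sets. A search through many recorded variables, each judged at 0.05, has a chance of a false factor well above 0.05. A trial of this size also has little power for factors of moderate strength. The small sample does not itself raise the false-positive rate. It lowers power, so a larger share of the factors declared would be false, and true factors that reach significance would tend to be overestimated.

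At stake is whether the trial reports as determined something that it can only suggest.

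**Working it through.** **1. Number of patients.** Inputs from section 2.3: reference proportion 28.6%, expected proportion 50%, alpha 0.10, power 0.80, dropout 10%. The plan does not state the sidedness or the formula. With the one-sample arcsine formula and one-sided alpha:

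- h = 2·arcsin(√0.50) − 2·arcsin(√0.286) = 0.4423
- n = [(1.2816 + 0.8416) / 0.4423]² = 23.05, rounded up to 24
- 24 / 0.9 = 26.7, rounded up to 27

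This reproduces the planned 27, with about 24 evaluable. Baseline associations could use all 27.

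**2. Contributory factors.** This step needs no arithmetic. Section 2.2 fixes one arm, and section 2.5 compares each patient's status at the start with that at 8 or 16 weeks. Observed change = stimulation effect + spontaneous change + retest change. A variable's association with the sum does not identify its association with the first term.

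**3. Chance of at least one false factor.** The number of tests and their correlation are assumptions. Fourteen variables can be counted from section 2.4: height, weight, body mass index, grip, calf circumference, disease duration, alcohol, smoking, blood pressure, heart rate, oxygen saturation, rating-scale score, tongue pressure and peak expiratory flow. One search gives k = 14. A second search over the same variables, for response, gives k = 28.

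For independent null tests the chance is 1 − 0.95^k: 1 − 0.95^14 = 0.51 and 1 − 0.95^28 = 0.76. For correlated tests, equicorrelated normal statistics were simulated (400,000 draws, two-sided 0.05):

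| Tests | ρ = 0 | ρ = 0.3 | ρ = 0.5 | ρ = 0.8 |
|---|---|---|---|---|
| 14 | 51% | 44% | 35% | 20% |
| 28 | 76% | 64% | 49% | 25% |

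The range is 20% to 76%, or about 4 to 15 times 0.05. All entries assume that no variable is truly associated.

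**4. Detectable difference.** Two-sample t-test, two-sided 0.05, 80% power:

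| Split | Total | Detectable difference | Power at 0.5 SD |
|---|---|---|---|
| 13 v 14 | 27 | 1.12 SD | 24% |
| 12 v 12 | 24 | 1.20 SD | 22% |
| 8 v 19 | 27 | 1.23 SD | 21% |
| 7 v 17 | 24 | 1.32 SD | 19% |

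The unequal splits apply 28.6% to the total (24 × 0.286 = 6.9; 27 × 0.286 = 7.7). That figure is a normal-cough rate from preliminary tests in neurodegenerative disorders, so it only illustrates an uneven split. The actual split by dysphagia or by response is unknown.

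**The case against.** The strongest reply is that the article already calls the study exploratory, single-arm and small, in the same Discussion that contains the promise. The aim in section 2.2 is worded as association, and contributory factors of the stimulation appear in only one Discussion sentence. Nothing in Table 2 depends on them. All of this is true, and it is why the point is minor. It does not dispose of the point. A general caveat does not make the second claim attainable, and it does not take these analyses out of the p<0.05 rule.

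Three stronger readings are tempting and are not supported:

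- **That a false factor is likely.** Most of the figures above are below 50%. For a single search of 14 variables, one half is passed only near zero correlation, which is implausible when body mass index is computed from height and weight. Any truly associated variable also reduces the number of null tests.
- **That the plan sets out to test every recorded variable.** Section 2.4 is a list of data to be recorded. Applying the section 2.5 rule to each item is an inference from the only criterion given.
- **That the plan is deficient because it gives no candidate list, no multiplicity rule and no Table 2 entry for these analyses.** Such detail is commonly left to a full protocol or analysis plan, which is not shown here. It forms no part of this point.

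**Conclusion.** The point holds as a minor one. That a single-arm design cannot determine contributory factors of the stimulation follows from the design and rests on no numerical assumption. That the wording about determining or identifying is too strong for both sets rests on applying the stated p<0.05 rule to the recorded variables. Under 14 to 28 null tests with correlation 0 to 0.8, the chance of at least one false factor is about 20% to 76%, and only differences of roughly 1.1 to 1.3 SD would be detected with 80% power. The primary, secondary and safety endpoints are untouched.

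**What to change.** In sections 2.2 and 3, replace identify and determine, where they refer to factors, with explore. In section 3, replace contributory factors of the stimulation with factors associated with change. In section 2.5, state that the p<0.05 significance rule does not apply to these analyses, and that effect estimates with 95% CIs will be reported for all factors examined, together with how many were examined.

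The change is to wording only and needs no new patients or data. The cost is that a single factor reaching p<0.05 can no longer be claimed as determined.

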## Data statement

The data supporting this study's findings will be available from the corresponding author upon reasonable request.
